## Abstract

**Background:**

There is a strong need to improve medication adherence (MA) for individuals with hypertension in order to reduce long-term hospitalization costs. We believe this can be achieved through an artificial intelligence agent that helps the patient in understanding key individual adherence risk factors and designing an appropriate intervention plan. The incidence of hypertension in Sweden is estimated at approximately 27%. Although blood pressure control has increased in Sweden, barely half of the treated patients achieved adequate blood pressure levels. It is a major risk factor for coronary heart disease and stroke as well as heart failure. MA is a key factor for good clinical outcomes in persons with hypertension.

**Objective:**

The overall aim of this study is to design, develop, test, and evaluate an adaptive digital intervention called iMedA, delivered via a mobile app to improve MA, self-care management, and blood pressure control for persons with hypertension.

**Methods:**

The study design is an interrupted time series. We will collect data on a daily basis, 14 days before, during 6 months of delivering digital interventions through the mobile app, and 14 days after. The effect will be analyzed using segmented regression analysis. The participants will be recruited in Region Halland, Sweden. The design of the digital interventions follows the just-in-time adaptive intervention framework. The primary (distal) outcome is MA, and the secondary outcome is blood pressure. The design of the digital intervention is developed based on a needs assessment process including a systematic review, focus group interviews, and a pilot study, before conducting the longitudinal interrupted time series study.

**Results:**

The focus groups of persons with hypertension have been conducted to perform the needs assessment in a Swedish context. The design and development of digital interventions are in progress, and the interventions are planned to be ready in November 2020. Then, the 2-week pilot study for usability evaluation will start, and the interrupted time series study, which we plan to start in February 2021, will follow it.

**Conclusions:**

We hypothesize that iMedA will improve medication adherence and self-care management. This study could illustrate how self-care management tools can be an additional (digital) treatment support to a clinical one without increasing burden on health care staff.

**Trial Registration:**

ClinicalTrials.gov NCT04413500; https://clinicaltrials.gov/ct2/show/NCT04413500

**International Registered Report Identifier (IRRID):**

DERR1-10.2196/24494

## Introduction

### Overview

Hypertension is a common, dangerous, and treatable but undertreated condition worldwide and has a prevalence of approximately 30% in adults [1]. It becomes more common in more advanced ages, and the prevalence increases to 60% in persons over 60 years of age [2]. However, about 33% of persons with hypertension are unaware of their condition [2-4]. The incidence of hypertension in Sweden is estimated at approximately 27% [5]. Although blood pressure (BP) control has increased in Sweden, barely half of the treated patients achieved adequate BP levels [6].

Hypertension causes increased mortality and morbidity, most often by congestive heart failure, ischemic heart disease, and ischemic and hemorrhagic cerebrovascular insults [7]. Hypertension is also associated with increased occurrence of peripheral vascular disease and chronic kidney disease [8,9].

According to the National Board of Health and Welfare in Sweden [10], support and motivation for lifestyle changes as well as for self-care management are the first options when a person is diagnosed with hypertension, that is, having a systolic BP >140 mm Hg and diastolic BP >90 mm Hg measured repeatedly several times (3-6) over weeks or months, after 5 minutes of rest, while sitting with the right arm at heart level [10-12].

Lifestyle changes such as reducing weight, quitting smoking, reducing alcohol, and increasing physical activity are usually supported by visits to the district nurses individually or in groups in order to lower the BP. The support consists of educational and behavioral strategies to motivate and facilitate the person to conduct lifestyle changes in daily life [10]. If the lifestyle changes do not give results in lowering the person’s BP, medication treatment is required.

### Low Adherence to Medication

The World Health Organization defines adherence to long-term therapy as “the extent to which a person's behavior—taking medication, following a diet, and/or executing lifestyle changes—corresponds to agreed recommendations from a health care provider” [13]. In this work, we focus specifically on adherence to a medication regimen to improve BP control.

Although there are several effective medications that prevent cardiovascular events, persons can have poorly regulated BP. The main reasons for poor regulation of BP include patients’ lack of adherence to treatment and a lack of monitoring and intervention on the part of the doctor [2,14,15].

Adherence to the medication has been shown to be deficient. As an example, an analysis of pharmacy records has demonstrated that less than 50% of the study population had collected prescribed medications intended for hypertension [2]. Adherence to treatment is affected by many factors, including polypharmacy (ie, the number of tablets prescribed for hypertension), practical difficulties (eg, managing treatment costs, forgetfulness), and personal impressions affecting adherence (eg, side effects of medications) [16].

### Factors Affecting Adherence

Previous studies have linked both intrinsic and external factors to low or poor medication adherence (MA). Intrinsic factors include demographics such as age and income [17,18]. Psychological determinants include perceived susceptibility [19,20] and trust in the care provider [21,22], and behavioral factors include forgetfulness [19,23], employment, and travel [23]. External factors include the number of medications prescribed [18], availability of prescribed medication [23], and family support [18].

### Intervention Strategies That Improve Medication Adherence

A person's adherence can be improved by affecting the person's habit patterns in concurrence with the medication administration [24]. With BP monitoring at home, provision of adequate feedback, and improvement of cooperation between the person and health care personnel, the likelihood of the person retrieving their medication at the pharmacy increases [25].

There are several recommended approaches to address MA. Education strategies directed to the person have been shown to be of great importance [26]. Several studies have reported that health literacy levels may predict MA [27-29]. Behavioral strategies are important interventions to improve adherence to medications [26,30]. These strategies can vary and include unit-dose packaging, self-monitoring of medication, self-monitoring of symptoms or side effects, reminders, and other cues to action such as associating medication-taking with other daily activities.

Educational and behavioral strategies are highlighted in guidelines but are lacking in how to support the persons to improve MA [30]. In general, interventions successful in improving BP control and increasing MA are ones that improve awareness of and involvement in the treatment [31].

### Digital Interventions for Medication Adherence

Modern technologies make it possible to reach a vast number of persons using few personnel resources. With the widespread use in Sweden of the Internet and smartphones (93.1% internet penetration [32]), there are opportunities to use digital interventions, in specific to support people with hypertension on a wide scale and at low cost.

The authors have performed a systematic review recently on studies that applied digital interventions in order to improve BP and MA during the past decade [33]. The results show that digital interventions were effective in that regard, and the main targeted behaviors to change were lifestyle management, medication intake, self-measurement, and patient-provider interaction.

### Problem Formulation

Despite the availability of effective medications and the prior success of digital interventions, nonadherence to medications still remains a problem for some persons with hypertension. One of the common limitations of digital interventions is that they may be effective in changing the user’s current behavior but cannot adapt to the user’s changing needs over time. Most of the existing digital interventions provide a general solution for their users, and the user himself or herself is responsible for finding the right information or intervention. These digital interventions generally do not consider the barriers causing patients’ nonadherence (and other related behaviors) and their needs over time.

In a previous paper [33], the authors revealed the need to design a multifaceted digital intervention that can be personalized according to one or more patient behaviors that need to be changed to overcome the key determinant or determinants of low adherence to medication or uncontrolled BP among patients with hypertension, considering different levels including patient and health care team and system involvement.

The aim of this study is to design, develop, test, and evaluate a tailored digital intervention, to be delivered through a mobile app, to increase MA and self-care management for persons with hypertension.

## Methods

### Study Design

The design of the study is influenced by the intervention mapping technique [34], which is used for the design and development of health promotion programs. We decided to accomplish such a big study in smaller steps, as follows.

#### Systematic Review

We first conducted a systematic review in order to detect the determinants, behaviors to change, and implemented digital strategies in previous studies [33]. The literature review included key determinants for MA among persons with hypertension. From this review, we have extracted a list of target behaviors and psychological determinants to create an encompassing Matrix of Change Objectives. It reviews digital interventions for persons with hypertension in order to determine which intervention strategies have been employed previously for each combination of behavior and determinant in the Matrix.

#### Focus Groups

We conducted focus groups to ascertain the needs of persons with hypertension in a Swedish context and in relation to the findings of the conducted systematic literature review. The focus groups helped us to determine whether literature findings are applicable to our target population in a Swedish context, whether some key factors must be added or removed from our Matrix of Change, and whether the identified intervention options are applicable and in which order of preference. We will also conduct focus groups after the pilot study to verify the participants’ comprehension of the 16-item Maastrict Utrecht Adherence in Hypertension (MUAH-16) questionnaire regarding MA for hypertension (see Distal Outcomes), translated to Swedish, and also to perform the usability test for the mobile app.

#### App Design

Through what has been learned with the above findings, adaptive digital interventions are designed and developed to be delivered via mobile app.

#### Pilot Study

The pilot intervention will be conducted in order to evaluate the feasibility and usability of the proposed app for 2 weeks with the same group that attended the focus groups.

#### Longitudinal Study

The longitudinal study is designed to assess the effect of the proposed adaptive digital interventions delivered through the mobile app with individuals with hypertension for 6 months. The design is proposed to be an interrupted time series approach, which is considered to be the strongest quasi-experimental design that can be used to evaluate the effectiveness of an intervention [35,36]. The interrupted time series designs start to collect outcome measures before, during, and after intervention steps. Therefore, they are supposed to capture the level and any trend changes of one or more outcomes through time.

We will keep track of multiple variables for each participant through time and try to deliver the right intervention to the right person through patient-reported measures and app usage.

Two arms are considered in this design: One arm receives digital intervention. We will also add a nonequivalent no-treatment arm. This control group will be picked out of the group of patients who fulfilled the inclusion criteria and for whom the only criteria that are available for comparison is the primary MA (ie, pickups from the pharmacy). The reason to add this control group is to be able to address the internal validity threat [37]. By adding the control group, the effect of history is mitigated, and the study is strengthened against other threats to internal validity such as maturation (does the MA improvement occur naturally over time?).

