#### Longitudinal Study

The data from the participants in the study are sent through their mobile app to the server, where all the participants’ data is stored. All the data from the participants are collected via self-reports and their hypertension-relevant information in the aggregated health database. The only item that we measure without the participants’ engagement is if they have seen the intervention and how long it took to answer the questions. This information is used to measure the user’s fatigue and intervention retention and will be used to adapt the interventions.

The effect of the intervention is analyzed statistically using segmented regression analysis, testing for changes in both the level and the trend of the outcome.

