#### Distal Outcomes

Distal outcome is the ultimate goal that the intervention is trying to achieve. In iMedA, we considered primary and secondary distal outcomes. Primarily, we aim at improving MA. Then, in the long term, BP is considered as a secondary distal outcome along with increased quality of life [42], assessment of the lifestyle behavior (smoking, alcohol consumption, physical activity, and food intake) [10], and communicative and critical health literacy [43].

In order to measure MA, we consider the following:

Self-reported medication intake through the mobile app is supposed to be collected every day.MUAH-16 [44] is measured before and after the intervention. It is a MA questionnaire for hypertension. It consists of 16 items with four factors: (1) positive attitude towards health care and medication, (2) lack of discipline, (3) aversion toward medication, and (4) active coping with health problems. The items are on a 7-point Likert scale (1=completely disagree to 7=completely agree). A previous study [44] had found correlations between adherence and the MUAH-16 score. Specifically, they found that higher scores in subscale 1 correlated positively with adherence, and higher scores on subscale 2 correlated negatively with adherence.Pickups from pharmacies will be collected after the intervention is finished.

BP is to be measured once before the start of the intervention, at 3 months, and then at 6 months by the recruited nurse.

Health literacy will be measured by the Swedish Communicative and Critical Health Literacy scale. It consists of 5 items with a 5-point Likert scale [43]. Health status will be measured by EQ-5D (EuroQol 5-Dimension questionnaire). It consists of 5 areas for covering health, with 5 response alternatives and 1 overall question regarding health (EQ-VAS [EuroQol visual analogue scale] with score range of 0 to 100) [42]. Both will be measured before and after the intervention.

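### The control arm supplies only pharmacy pickups, so the claimed protection against history and maturation does not reach daily intake, MUAH-16, blood pressure, EQ-5D or health literacy

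*Protocol article*

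**What the plan says.** Under Study Design, Longitudinal Study, the article describes two arms: "We will also add a nonequivalent no-treatment arm". Its members are patients "for whom the only criteria that are available for comparison is the primary MA (ie, pickups from the pharmacy"). Two sentences later it says: "By adding the control group, the effect of history is mitigated, and the study is strengthened against other threats to internal validity", and gives maturation as an example of those threats. The sentence is not limited to any outcome.

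The Abstract (Methods) sets out the data collection: "We will collect data on a daily basis, 14 days before, during 6 months of delivering digital interventions through the mobile app, and 14 days". The last of these periods follows the end of the intervention, and the analysis named there is segmented regression. Data Collection and Analysis, Longitudinal Study, adds: "The effect of the intervention is analyzed statistically using segmented regression analysis, testing for changes in both the level and the trend of the outcome". Neither place names the outcome, and neither mentions the control arm. Decision Rules defines the pre-intervention phase as the first 14 days after the app is installed.

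Distal Outcomes lists three adherence measures: daily self-report in the app, MUAH-16 before and after, and pickups. On the last it says: "Pickups from pharmacies will be collected after the intervention is finished". A nurse measures blood pressure before the start, at 3 months and at 6 months. EQ-5D and health literacy are taken before and after.

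**The concern.** A control group protects a result against history and maturation only if it supplies the same outcome over the same period. Here the protection is claimed for the study as a whole, while the controls supply one outcome, and the text does not connect that outcome to the segmented regression. The series that fits the described phases exists only for app users.

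What is at stake is how the results may be read. The longitudinal study was due to start in February 2021, and the article itself cites disruption from COVID-19. An external change near the start of the intervention would appear as an effect on daily intake or blood pressure, and a reader of the design section would believe that the control arm guards against this.

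**Working it through.** **1. Which outcomes have a control series?**

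| Outcome | Intervention arm | Control arm |
|---|---|---|
| Daily intake | self-report in app, daily | none |
| MUAH-16 | before and after | none |
| Blood pressure | before, 3 and 6 months | none |
| EQ-5D, health literacy | before and after | none |
| Pharmacy pickups | collected after the intervention | yes |

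The control column follows from "the only criteria that are available for comparison is the primary MA (ie, pickups from the pharmacy").

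**2. Which outcome fits the regression?** It needs daily points and a 14-day pre-phase from app installation. Of the three adherence measures only app intake is daily. Pickups do not fit that scale. At an assumed 30 to 90 days' supply, expected pickups per person in 14 days are 14/30 = 0.47 to 14/90 = 0.16. For 50 people that is 50 × 14/30 = 23 to 50 × 14/90 = 8. Intake in the app is therefore the likely outcome, by inference.

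**3. The plan's own figure.** Sample Size gives at least 32 participants in the intervention group, from simulations in a cited source. It cannot be reproduced: the baseline rate, level change, number of time points and exact autocorrelation are not given. The step from 32 to 50 implies 1 − 32/50 = 36% attrition. No power is stated for a contrast between arms.

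**4. Effect of an external shift (illustration).** Assumed: true adherence 0.80, no app effect, 14 pre-intervention and 182 intervention days, AR(1) errors with daily SD √(0.8 × 0.2/N), and a level shift starting exactly with the intervention. Level change was tested two-sided at 5%, with 1,000 runs per setting. Rejection rates for the single series:

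| N | Autocorrelation | No shift | 5 points | 10 points |
|---|---|---|---|---|
| 50 | 0.4 | 4.4% | 21% | 60% |
| 50 | 0 | 5.6% | 31% | 82% |
| 32 | 0.4 | 5.3% | 13% | 41% |
| 32 | 0 | 5.2% | 20% | 66% |

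With a control series of the same outcome that shares the shift, rejection stays between 3.7% and 5.8% in every setting.

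**5. How well do 14 days fix the prior trend?** For 50 participants and independent days, SD = √(0.16/50) = 0.0566 and the sum of squares of time is 14 × (14² − 1)/12 = 227.5. The standard error of the slope is 0.0566/√227.5 = 0.00375, or 0.375 points per day. The 95% half-width is 1.96 × 0.375 = 0.735 points per day. Carried forward 14 days, that slope uncertainty alone is 14 × 0.735 = about 10 points. Positive autocorrelation would widen this; stable differences between people would narrow it.

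**6. Power of a two-arm contrast (illustration).** Anchor at 80% power for 32 in a single series, so the standardised effect is 1.960 + 0.842 = 2.802. An equal-variance control divides it by √2.
- 32 per arm: 2.802/√2 − 1.960 = 0.021, power about 51%.
- 50 per arm: 2.802 × √(50/32)/√2 − 1.960 = 0.516, power about 70%.
- 80% needs 2 × 32 = 64 per arm.

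Pickups are a different outcome, so these figures show direction only.

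**The case against.** The limit on the control data stands two sentences before the claim, and the maturation example that follows refers to adherence. Read together, the paragraph may mean only that the pickup comparison is protected. No passage says that blood pressure or MUAH-16 is controlled. This softens the point, but the claim is still worded for the whole study.

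Several stronger readings are tempting, and the text does not support them:

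- *The regression is certainly of app data, with no arm term.* The outcome is not named. The article also draws on an aggregated health database and speaks of two arms within this design. Arm terms are the kind of detail a journal article condenses.
- *Pickups exist only after the intervention.* The sentence gives the time of extraction, not the period covered. A dated retrospective series in both arms is not ruled out.
- *Natural drift passes straight into the effect.* Segmented regression measures change against the prior trend, so linear drift is handled in principle. The weakness is how poorly 14 days estimate that trend.
- *An external shift always biases the estimate by its full size.* That requires the shift to coincide with each participant's start. The pre-phase is counted from each participant's installation, and nothing says that all start together. With staggered starts a calendar shock is spread over participant time.

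What stands is a matter of data rather than model detail: no arm term can be fitted to an outcome that controls never supply.

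**Conclusion.** The point holds for daily intake, MUAH-16, blood pressure, EQ-5D and health literacy: the article claims a protection that the design does not give them. For pickups the claim can hold in part. The arm is nonequivalent, with app participants compared against patients picked from the eligible pool, so differences in selection remain. A reader might infer that the whole study is uncontrolled; it is not, since a controlled pickup analysis remains possible.

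The rejection rates of 13% to 82% rest on an assumed adherence level, assumed shifts of 5 to 10 points and exact coincidence with the intervention start. They show direction and possible size and are not a forecast. That the regression outcome is app intake is a strong inference and not a stated fact. This should be fixed, because it changes what the trial can conclude. The remedy is clarification and one added analysis, not a redesign.

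**What to change.** 1. Name the outcome of the segmented regression.
2. Extract dated pickups for both arms over a defined period before and after start, and give controls comparable calendar start dates. Estimate the effect by the arm-by-level and arm-by-trend terms. The look-back and adherence metric are the sponsor's choice, for example 12 months and monthly proportion of days covered.
3. Restrict the history and maturation sentence to that analysis, and note that the nonequivalent arm gives partial protection.
4. Label daily intake, MUAH-16, blood pressure, EQ-5D and health literacy results as uncontrolled.

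The cost is a wider date range in the register extract, some protocol wording, and weaker claims for the app-based and blood pressure outcomes. The precision expected from the two-arm pickup contrast should also be stated, since the figure of 32 does not address it.
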